#### Economic outcomes

To inform whether it is cost-effective to incorporate FP-CPAP or Seattle-PAP into the existing health system, a decision analysis will be constructed based on the primary outcome and associated hospital costs. Univariate and probabilistic sensitivity analyses will be conducted to test the impact of uncertainty in the data. We will first compare the mean patient-level costs for each treatment arm, without consideration of effectiveness. Because of the anticipated skewed nature of the cost data, we will model the logarithm of the mean costs directly, using a generalized linear model with a logarithmic link function and gamma distribution [24, 29]. In addition to treatment assignment, covariates will be entered into this model to account for any differences in baseline prognostic indicators (e.g., exposure to antenatal corticosteroids) that are evident despite randomization. The model will take into account clustering among twins.

We will then determine the simultaneous outcome of cost and effect, or value for money, expressed as the incremental cost-effectiveness ratio, which is calculated as the difference in mean cost per patient in the Seattle-PAP and FP-CPAP groups divided by the difference in the mean effect between the two groups. We will determine the statistical uncertainty in the joint distribution of costs and effects using nonparametric bootstrapping, in which we will draw 1000 samples of 220 infants, with replacement, from the study data set [30, 31]. For each of the 1000 samples, we will calculate the mean cost, mean effect, and incremental cost-effectiveness ratio. The results of this analysis will be presented using an incremental cost-effectiveness plot and cost-effectiveness acceptability curves [32]. Parameter uncertainty, for variables such as price weights, will be estimated using a deterministic sensitivity analysis, in which the results are generated again after varying the parameter through its plausible range [30].

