#### Randomization

Enrolled eligible infants are randomly assigned to one of two treatment arms (Seattle-PAP vs. FP-CPAP) (Fig. 3). The allocation sequence is generated using an online, computer-generated randomizer (https://sealedenvelope.com), with a block size of 6, stratified by GA (27–29^6/7^ and 22–27 weeks’ GA). We did not stratify by site, as the treatment of premature neonates is based on shared guidelines throughout the NCH-NRN [23]. Multiple gestations (twins or triplets) are assigned to the same treatment arm.

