#### Sample size

Using data from other recent large neonatal randomized trials with similar populations, including the SUPPORT trial and the COIN trial [9, 10], as well as contemporary data within the NCH-NRN, we estimate that the proportion of patients experiencing respiratory failure in the control arm (FP-CPAP) will be 50%. Based on preclinical work, we estimate the failure rate in the Seattle-PAP arm will be 30% [13, 17]. Accounting for two interim analyses, 200 neonates are needed with a two-tailed type I error rate of 0.05 and a power of 80% [25]. Multiples will be randomized as a set to the same study arm, requiring an inflation of the estimate by 1.12 to allow for the design effect due to clustering [26, 27]. Thus, the calculated sample size is 115 infants per treatment arm.

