### Statistical analysis

#### Clinical outcomes

Analyses will be performed using Statistical Analysis Software (SAS) Enterprise Guide version 7.15 (SAS Institute Inc., Cary, NC, USA) using an as randomized (intention-to-treat) principle to compare the primary outcome between treatment arms. Continuous data will be expressed as means with standard deviations or as medians with ranges, whereas categorical variables will be expressed with frequencies and proportions. The primary outcome, and other binary outcomes occurring in at least 5% of patients, will be analyzed using Pearson chi-squared tests. Less common binary outcomes will be compared using Fisher’s exact tests. Risk differences and the number needed to treat, along with their 95% Newcombe hybrid score confidence intervals will be calculated, and risk ratios, and their 95% Koopman asymptotic score confidence intervals, will also be calculated. Normally distributed, continuous outcomes will be compared using Student’s *t*-test, whereas the Wilcoxon rank-sum test will be used to compare continuous outcomes with skewed distributions.

In additional analyses, log binomial regression models will be used to evaluate heterogeneity in the effect of treatment with Seattle-PAP on the primary outcome. Treatment effect heterogeneity will be explored across several clinical characteristics that are known to be associated with CPAP treatment failure: GA, birth weight, and exposure to antenatal corticosteroids [15]. Treatment effect heterogeneity will be tested by evaluating the significance of interactions between the factors of interest and treatment arm in log binomial regression models that include the factor, treatment arm, and their interaction. Effect estimates within subgroups defined by these factors will be expressed as risk ratios with maximum likelihood-based 95% confidence limits. Regression models will be estimated using generalized estimating equations to account for the inherent correlation expected with multiples [27].

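### The cost model picks its covariates by observed baseline imbalance, which costs precision in the adjusted cost comparison and tends to leave out gestational age

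*Protocol article*

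**What the plan says.** Economic outcomes opens with a comparison of mean patient-level costs by arm, "using a generalized linear model with a logarithmic link function and gamma distribution". Beyond treatment, covariates enter this model "to account for any differences in baseline prognostic indicators (e.g., exposure to antenatal corticosteroids) that are evident despite randomization". Antenatal corticosteroid exposure is the only example. The section gives no closed list and does not say what counts as evident. It does say that clustering among twins will be taken into account.

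Two other sections bear on this. Clinical outcomes names three characteristics "known to be associated with CPAP treatment failure: GA, birth weight, and exposure to antenatal corticosteroids" and plans heterogeneity analyses on them. Randomization says that allocation is done "with a block size of 6, stratified by GA", in two strata.

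**The concern.** Under randomisation, baseline differences arise by chance, and the unadjusted standard error already allows for them. The reason to adjust is that a covariate predicts the outcome, because adjustment then removes outcome variance whether or not the arms happen to differ. A rule triggered by imbalance has three consequences:

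- It omits strong predictors that happen to balance. Stratified allocation makes GA balance by design, so the rule works against the very factor the trial chose to control.
- The analysis switches between two models according to the data, so the test no longer runs at its nominal level.
- With no criterion for what is evident, the covariate set can be settled after the baseline table has been seen.

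At stake is the precision and credibility of the adjusted cost difference.

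**Working it through.** **Inputs from the protocol.** 115 infants per arm (Sample size), the gamma/log-link model and the imbalance rule (Economic outcomes), and GA stratification (Randomization). The protocol gives no figure for the cost model. Its 115 per arm comes from the primary outcome: 50% against 30%, two-sided 5%, 80% power, with continuity correction, gives 103 per arm, and 206 × 1.12 = 230.7. From the stated 200, 200 × 1.12 = 224. Either is within 3% of 230, so 115 per arm is used below.

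**Assumptions, not in the protocol.** The strength of the covariates for cost (R² on the log scale), and *evident* taken as a baseline test at p<0.05. Clustering of multiples is ignored.

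**Step 1: strong covariates, by hand.** Take three independent standard-normal covariates with coefficients 0.4, 0.4 and 0.3 for log cost, and residual SD 0.75. Covariate variance is 0.16 + 0.16 + 0.09 = 0.41, residual variance is 0.5625, and R² = 0.41/0.9725 = 0.42. The SD of the treatment estimate is:

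- always adjusted: 0.75 × √(2/115) = 0.099
- never adjusted: √(0.9725 × 2/115) = 0.130
- imbalance rule: a covariate is left in the error only when its standardised imbalance z satisfies |z|<1.96. The share of its variance that remains is 0.95 − 2 × 1.96 × 0.0584 = 0.721. So √((0.5625 + 0.721 × 0.41) × 2/115) = 0.122

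The ratio is 0.122/0.099 = 1.23. Simulation of 20,000 null trials gives the same SDs (0.099, 0.130, 0.122), with type I errors of 5.0%, 4.9% and 3.7% in that order. Repeat runs put the rule at 3.8% and 3.9%, and fixed adjustment at 5.1%.

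**Step 2: range over covariate strength and stratification.**

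| Setting (trigger p<0.05) | SD, rule vs fixed | Ratio | Type I error, rule |
|---|---|---|---|
| R² 0.42, unstratified | 0.122 vs 0.099 | 1.23 | 3.7–3.9% |
| R² 0.42, stratified on one covariate | 0.119 vs 0.099 | 1.20 | 3.2–3.3% |
| R² about 0.1 | 0.130 vs 0.127 | 1.02 | 4.5–4.8% |

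**Step 3: one covariate, normal model.** At R² of 0.1, 0.2, 0.3 and 0.5, the rule's type I error is 4.9%, 4.3%, 4.1% and 3.6% with trigger p<0.05. With trigger p<0.20 it is 4.5%, 3.9%, 3.3% and 2.4%. Fixed adjustment stays at 4.8–5.2%. The fixed-to-unadjusted SE ratio should be √(1 − R²) = 0.95, 0.89, 0.84 and 0.71; simulation gives 0.95, 0.90, 0.84 and 0.71. Where unadjusted power is 80%, fixed adjustment gives 84%, 88%, 91% and 97%, against 80–82% under the rule.

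**Step 4: the planned model with GA-stratified allocation.** Gamma GLM, shape 3, 85% steroid exposure with coefficient −0.2, GA coefficient −0.3 or −0.5 per roughly one-SD unit, and a treatment effect of −0.25 on the log scale for power.

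| GA coefficient | Type I error: none / rule / fixed | Power: rule vs fixed |
|---|---|---|
| −0.3 | 3.7% / 3.6% / 4.7% | 82% vs 90% |
| −0.5 | 2.6% / 2.7% / 5.1% | 67% vs 90% |

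The rule performs almost exactly like no adjustment. The trigger rates show why. Two covariates tested at 5% should trigger in 1 − 0.95² = 9.75% of trials, and without stratification they did so in 10.0% and 9.3%. With stratification the rate fell to 4.8% and 5.4%, which is what steroid exposure alone would produce. GA practically never enters.

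**Step 5: reach of the rule.** Economic outcomes assigns the covariate model to the cost comparison made before effectiveness is considered. The incremental cost-effectiveness ratio is then defined from differences in per-patient means, and each bootstrap sample yields a mean cost, a mean effect and their ratio. The adjusted model is not named in that step. Clinical outcomes tests the primary outcome by an unadjusted chi-squared test.

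**The case against.** **Condensed article.** A covariate list and a definition of evident imbalance can properly sit in a fuller economic analysis plan, so their absence is not a fault. This stands. The principle of selecting by imbalance is stated, however, and a fuller plan that follows the sentence would carry it forward.

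**Direction of error.** A reader might infer that a miscalibrated test means extra false positives. The calculations do not support that: under a mechanical rule the error is below 5% in every scenario run. Discretionary choice could push it either way, but nothing in the protocol lets that be quantified. The Blinding section keeps the analysing statisticians blind to group assignment, which softens the worry about discretion without restoring the lost precision.

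**Reach.** A reader might also infer that the cost-effectiveness ratio, the acceptability curves or the primary result are compromised. The text does not support this, as Step 5 shows.

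**Premise about cost.** The protocol nowhere says that GA drives cost. Clinical outcomes links "GA, birth weight, and exposure to antenatal corticosteroids" to CPAP failure, and the Background links failure to higher daily costs and longer stay. That these factors predict cost is a reasonable inference, not a stated fact. If they predict it only weakly, the loss is about 2%.

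**Conclusion.** The point holds as a badly chosen covariate rule in one secondary analysis. With a p<0.05 trigger and R² of about 0.1 to 0.4 on the log-cost scale, both assumed, the test runs at about 3% to 5% where 5% is intended. The treatment estimate's SD is about 2% to 23% larger than with fixed covariates. The loss is small if the covariates are weak and material if they are strong, and GA stratification makes omission of GA close to certain. The trial's main clinical conclusion does not depend on this rule. It is worth correcting because the correction is nearly free, not because the result is in danger.

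**What to change.** Replace the imbalance rule in Economic outcomes with a fixed set, for example:

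> The cost model will include treatment, gestational-age stratum, birth weight and antenatal corticosteroid exposure, regardless of observed balance, accounting for clustering of multiples.

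The change is one sentence and should be made before the cost data are analysed. GA, birth weight and steroid exposure are already needed for the planned heterogeneity analyses, so no new data are required. With a log link and no treatment-by-covariate interaction, the ratio of mean costs keeps its meaning after adjustment. The price is three or so degrees of freedom out of 230 infants. Under the assumptions above, the test returns to close to its nominal level (4.7–5.8% across the simulations, the extremes being the gamma runs of 6,000 replicates).

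### The cost comparison is adjusted for baseline prognosis, but the ICER, bootstrap and acceptability curves are worded as plain arm means: valid, but less precise and not tied to the adjusted cost difference

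*Protocol article*

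**What the plan says.** All of this stands in the protocol article under Economic outcomes, unless another section is named.

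- **Step one, cost alone.** Mean patient-level costs are compared "using a generalized linear model with a logarithmic link function and gamma distribution". Besides treatment, "covariates will be entered into this model to account for any differences in baseline prognostic indicators"; antenatal corticosteroid exposure is the one example given. On multiples: "The model will take into account clustering among twins".
- **Step two, cost and effect together.** The ICER has this definition: "calculated as the difference in mean cost per patient in the Seattle-PAP and FP-CPAP groups divided by the difference in the mean effect". For uncertainty, "we will draw 1000 samples of 220 infants, with replacement, from the study data set". Then: "For each of the 1000 samples, we will calculate the mean cost, mean effect, and incremental cost-effectiveness ratio". Finally: "The results of this analysis will be presented using an incremental cost-effectiveness plot and cost-effectiveness acceptability curves".
- **Effect side.** Under Clinical outcomes: "The primary outcome, and other binary outcomes occurring in at least 5% of patients, will be analyzed using Pearson chi-squared tests". The primary effect is therefore unadjusted.
- **Allocation.** Under Randomization, the sequence uses blocks of 6 within two GA strata divided at 27 weeks.

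Step two names no model, covariate or stratum. It also does not call its means raw or unadjusted.

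**The concern.** The plan gives a reason to adjust cost for baseline prognosis, and then states an estimator for the ICER that does not carry the adjustment. Step one leaves effectiveness aside by design. Within this trial-based analysis, the value-for-money answer therefore comes from step two, the part with no stated adjustment.

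Three things are at stake:

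1. **Precision.** If GA and other baseline factors predict cost, plain means leave that variation in the incremental cost.
2. **Consistency.** The report would hold two incremental costs, one adjusted and one inside the ICER. They can differ in size, and in sign when the true difference is near zero. No rule says which one governs.
3. **Calibration of the bootstrap.** Stratified randomization removes part of the GA-related variation between arms. Resampling the whole data set without regard to strata puts it back, so the spread on the plane and the slope of the acceptability curve can show more uncertainty than the design carries.

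**Working it through.** **Plan figures.** The plan states no cost mean, cost SD or covariate R-squared, so it has no economic figure to reproduce. The one plan figure used is the sample size. For 50% v 30%, two-sided 0.05 and 80% power:

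- n per arm = [1.96 × √(2 × 0.4 × 0.6) + 0.8416 × √(0.5 × 0.5 + 0.3 × 0.7)]² / 0.2² = (1.358 + 0.571)² / 0.04 ≈ 93.
- With continuity correction, n = 103.
- 103 × 1.12 = 115.4, which agrees with the stated 115 per arm (230 in all).

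**Rule of thumb.** Without stratification, adjustment cuts the standard error by about 1 − √(1 − R²):

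- R² = 0.1: 1 − √0.9 = 0.05
- R² = 0.2: 1 − √0.8 = 0.11
- R² = 0.5: 1 − √0.5 = 0.29

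**Simulation without stratification.** 230 infants, gamma costs with CV about 0.7 within covariate level, one prognostic covariate, 600 trials per setting. The true cost effect was zero or about −10%. The adjusted estimate is the gamma/log-link difference standardized to the cost scale.

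| Assumed R² | SD raw / SD adjusted | Opposite signs |
|---|---|---|
| 0 | about 1.00 | 1-2% |
| about 0.08 | 1.05 | 5-12% |
| about 0.23 | 1.20-1.23 | 13-19% |
| about 0.38 | 1.51-1.59 | 16-25% |

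Both estimators were centred on the same value (for example −10.36 raw and −10.24 adjusted at R² about 0.08). The raw difference is not biased.

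**Simulation with the trial's GA stratification.** 230 infants, blocks of 6, no true cost difference, 1000 trials per setting. Assumptions: log-cost slope −0.2 per week of GA, 80% steroid exposure with a 10% effect on cost.

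| Residual cost CV | SD ratio, GA skewed to later weeks | SD ratio, GA uniform |
|---|---|---|
| 0.45 | 1.14 | 1.22 |
| 0.7 | 1.09 | 1.14 |
| 1.0 | 1.08 | 1.10 |

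- Without stratification, the skewed-GA setting at CV 0.45 gave 1.30, so stratification roughly halves the excess (0.30 to 0.14).
- Adjusting for steroids alone, in the same stratified setting at CV 0.45, gave a ratio of 0.99 and opposite signs in 3%. The gain comes from GA.
- Over slopes of 0.1-0.2 and CV 0.45-0.70, a further set of 600 trials per setting gave opposite signs in 8-17% with stratification and 11-25% without.

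Across the GA slopes and cost CVs tried with stratification, the raw SD was about 0-25% larger than the adjusted one.

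**Bootstrap spread.** The variance of the raw difference splits into a within-stratum part and a between-stratum part. Stratified allocation largely removes the second; resampling the whole data set estimates both. In simulation, the standard error that such resampling targets was 0-21% above the true SD of the raw difference, again depending on GA slope and cost CV. The error is towards too much uncertainty.

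**The case against.** The strongest case against has five parts.

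- **The text is open.** Step two never says raw or crude, and a difference in mean cost is the ordinary definition of an ICER. Model-based means could be carried forward from step one, and a condensed article may leave that to a fuller plan. This stands as a possibility. But the article does state what each replicate calculates, and adjustment is not part of it; a reader following it would compute arm means.
- **No validity problem.** Randomization makes the raw difference unbiased, and an unadjusted effect agrees with the unadjusted primary analysis. This stands in full. A reader might infer that the ICER is biased, or that chance imbalance would drive the economic conclusion. The documents do not support either inference: allocation is stratified by GA, and both estimators centre on the same value.
- **Size.** A reader might take a loss of 30% or more from calculations that leave out stratification. The trial's own design lowers it, and if covariates predict cost weakly it is close to nil.
- **Opposite signs.** Most of these figures assume no true cost difference, where either sign is noise. They show that the two reported numbers can disagree, not that the decision would be wrong.
- **Standing of the analysis.** The economic evaluation is ancillary, and the plan also lists a decision analysis with sensitivity analyses. This lowers the priority but does not settle which incremental cost enters the ICER.

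**Conclusion.** The point holds as a cheap improvement in precision and consistency, not as an error of validity. As worded, the plan adjusts cost for baseline prognosis in one analysis and builds the ICER, the 1000 replicates, the plot and the acceptability curves from plain means drawn without regard to the randomization strata.

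With GA stratification, the precision loss is about 0-25% in the SD of the cost difference, and the bootstrap can overstate the standard error of the raw difference by about 0-21%. Both ranges rest on assumed GA slopes, GA distributions and cost CVs, because the documents give none. They fall to nothing when the covariates do not predict cost.

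The difference between the planned resample size of 220 and the planned 230 infants, and the handling of multiples in the resampling, are separate matters not assessed here.

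**What to change.** In Economic outcomes:

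1. Name one prespecified covariate set for the economic analysis. It should include GA (the stratification factor) and antenatal steroids, and should not depend on which imbalances turn up.
2. Within each bootstrap replicate, refit the gamma/log-link cost model and a model for the primary outcome with the same covariates.
3. Standardize both fits over the sample to obtain the incremental cost and incremental effect. Build the ICER, the plane and the acceptability curves from these.
4. Report the raw-mean version, which matches the unadjusted primary risk difference, as a labelled sensitivity analysis.

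The cost is a few sentences and a few lines of code. GA and steroid exposure are already used in the planned analyses, and no infant's care changes. The downside is that the ICER becomes model-based and its effect denominator may differ slightly from the unadjusted primary risk difference; the sensitivity analysis shows by how much.

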**Methods/design:**

We designed a multicenter, non-blinded, randomized controlled trial that will enroll 230 premature infants (22^0/7^ to 29^6/7^ weeks of gestation). Infants will be randomized to receive Seattle-PAP or FP-CPAP. The primary outcome is respiratory failure requiring intubation and mechanical ventilation. Secondary outcomes include measures of short- and long-term respiratory morbidity and cost-effectiveness.

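### The cost-effectiveness bootstrap fixes 220 individual infants, but the trial plans 230 and randomises multiples as sets; the net effect is a standard error about 3.4% too narrow

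*Protocol article*

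**What the plan says.** All references are to the protocol article.

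- **Economic outcomes.** Uncertainty in the joint distribution of cost and effect is to come from a nonparametric bootstrap: "we will draw 1000 samples of 220 infants, with replacement, from the study data set". Mean cost, mean effect and the incremental cost-effectiveness ratio are calculated in each sample. The results feed the cost-effectiveness plot and the acceptability curves.
- **Abstract, Methods/design.** The trial is described as a "randomized controlled trial that will enroll 230 premature infants".
- **Sample size.** After an inflation of 1.12 for clustering of multiples, "the calculated sample size is 115 infants per treatment arm", which is 230 in total.
- **Randomization.** Twins and triplets go to the same arm as a set.
- **Clustering elsewhere.** The clinical regression models use generalized estimating equations to allow for correlation between multiples. For the gamma regression of costs, which comes before the bootstrap in the same section, the article says "The model will take into account clustering among twins". The description of the bootstrap has no such statement.

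**The concern.** A standard nonparametric bootstrap imitates the sampling process. It redraws the independent units of the design, and as many of them as were analysed. The stated procedure departs from this twice.

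**Size.** The article does not explain 220. It is not the 200 before inflation, nor 200 × 1.12 = 224, nor the planned 230. A resample smaller than the data set overstates the standard error.

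**Unit.** The stated unit is the infant, whereas the independent unit is the sibling set. Redrawing siblings as if unrelated understates the standard error when their outcomes are positively correlated, which the article expects. The sentence on twins belongs to the cost regression. It does not carry over to a bootstrap that works from raw means in each resample.

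At stake is the spread of points on the cost-effectiveness plot, and with it the stated probability that Seattle-PAP is cost-effective. The cost regression and the bootstrap would also attach different precision to the same cost difference, because only the regression allows for clustering.

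**Working it through.** **Inputs from the article:** failure rates 50% and 30%, two-sided type I error 0.05, power 80%, 200 infants before inflation, design effect 1.12, 115 per arm (all from Sample size); resample size 220 (Economic outcomes).

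**1. Is 230 the right comparator?** The usual two-proportion formula with pooled variance, z = 1.96 and 0.842, gives

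(1.96 × √(2 × 0.4 × 0.6) + 0.842 × √(0.25 + 0.21))² / 0.20² ≈ 93 per arm.

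With continuity correction this becomes (93/4) × (1 + √(1 + 4/(93 × 0.20)))² ≈ 103 per arm, or 206 in total, within 3% of the stated 200. Then 103 × 1.12 = 115.4 per arm, which reproduces the stated 115. So 230 follows from the article's own inputs. The bootstrap's 220 is 10 infants, or 4.3%, below it.

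**2. Effect of the size.** The bootstrap standard error (SE) scales with 1/√n. Drawing 220 from 230 multiplies it by √(230/220) = 1.022, about 2.2% too wide.

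**3. Effect of the unit.** With design effect D, infant-level resampling gives 1/√D of the correct SE. At D = 1.12 this is 1/√1.12 = 0.945, about 5.5% too narrow.

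**4. Together.** 1.022 × 0.945 = 0.966, about 3.4% too narrow.

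**5. Simulation check.** There were 115 infants per arm and a continuous outcome with SD 1. The twin share and intraclass correlation were assumed to be 30% with 0.4, or 24% with 0.5. Each pair gives D = 1.12, since for twins D = 1 + share × correlation (0.30 × 0.4 = 0.24 × 0.5 = 0.12).

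| Procedure | SE of the difference between arms |
|---|---|
| True sampling SE, simulated | 0.138 to 0.139 |
| 220 individual infants (as written) | 0.134 |
| 230 individual infants | 0.131 |
| Sibling sets, as many as analysed | 0.138 |

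These runs drew from both arms together. A further run that drew sibling sets within each arm also gave 0.138.

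**6. What this does to an acceptability curve.** Assume net benefit is approximately normal and divide the z-value of the true probability by 0.966. A true 80% is then reported as 80.8%, 90% as 90.8%, and 95% as 95.6%. The largest shift anywhere is about 0.8 percentage points. For comparison, the Monte Carlo error of a proportion from 1000 replicates, √(p(1 − p)/1000), is 1.3, 0.9 and 0.7 points at 80%, 90% and 95%.

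**7. Sensitivity to the design effect for costs.** The article gives none, so these values are assumptions. The net factor is √(230/220)/√D.

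| D | Net factor | Direction |
|---|---|---|
| 1.00 | 1.022 | 2.2% too wide |
| 230/220 = 1.045 | 1.000 | the two errors cancel |
| 1.12 | 0.966 | 3.4% too narrow |
| 1.25 | 0.915 | 8.5% too narrow; largest shift about 2 points |

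**The case against.** The strongest reply is that the one explicit contradiction, 220 against 230, is small and conservative: taken alone, it cannot make Seattle-PAP look more certain than it is. The clustering part is an inference from the resampling unit named in a condensed article, and an economic analysis plan may say how siblings are handled. The authors plainly know about clustering, since they allow for it in three other places. The net error is also within the Monte Carlo noise of 1000 replicates, and the evaluation is ancillary to the trial.

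Most of this bears on size, and on size it stands. It does not remove the point. The text is not merely silent: it names the infant as the unit and fixes the count. A fixed number of infants does not fit resampling of sibling sets, where the number of infants varies from draw to draw. The figure 220 might be an expected evaluable number, but the article does not say so, and a preset count should in any case give way to the number analysed.

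A reader might infer more than the article supports:

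- **That siblings share hospital course and cost.** The article supports a shared arm and an expected correlation, and gives no figure for costs.
- **That draws are pooled across arms, so that varying arm sizes are a fault.** The article does not say whether draws are made within arm. Varying arm sizes are a normal feature of an unconditional bootstrap and matter little near 115 per arm.
- **That the cost-effectiveness probability would be seriously misstated.** At the article's own design effect the shift is below 1 percentage point.
- **That the economic analysis ignores clustering altogether.** The cost regression allows for it; only the bootstrap, as described, does not.

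**Conclusion.** The point holds as a minor correction. The stated resample size conflicts with the planned enrolment, and the stated unit conflicts with the randomisation of sibling sets. At a design effect of 1.12 the bootstrap standard error would be about 3.4% too narrow.

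This rests on three assumptions: that enrolment reaches 230 and all are analysed, that resampling is by infant as the wording indicates, and that the 1.12 from the sample size calculation applies to cost and effect. The last is the weakest. With a design effect for costs below about 1.045 the net error turns conservative; with a larger one it grows.

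The two departures partly offset each other by accident, so a partial repair would do harm: correcting the size alone moves the error from 3.4% to 5.5% too narrow. The primary comparison, the trial's sample size and the safety monitoring are not affected.

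**What to change.** Delete the fixed 220 and rewrite the bootstrap sentence under Economic outcomes along these lines: in each of 1000 replicates, sibling sets (singletons counting as sets of one) are drawn with replacement within each treatment arm, as many sets as were analysed in that arm, and all infants in a drawn set are kept together with their costs and outcomes.

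This ties the resample to the data actually analysed, whatever the final enrolment, and brings the bootstrap into line with the cost regression. Drawing within arm keeps the number of sets per arm fixed. Resampling within gestational-age strata as well is optional and is not needed to repair the inconsistency.

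The cost is one sentence and a few lines of code, with no new data and no change to the design. The price is slightly wider intervals: at the design effect of 1.12, by a factor of 1/0.966 = 1.035.
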